# TULIP: a randomised controlled trial of surgical versus non-surgical treatment of lateral compression injuries of the pelvis with complete sacral fractures (LC1) in the non-fragility fracture patient—a feasibility study protocol

**DOI:** 10.1136/bmjopen-2019-036588

**Published:** 2020-02-10

**Keywords:** trauma management, adult orthopaedics, orthopaedic & trauma surgery

## Abstract

**Introduction:**

Lateral compression type 1 (LC1) pelvic fractures are the most common type of pelvic fracture. The majority of LC1 fractures are considered stable. Fractures where a complete sacral fracture is present increases the degree of potential instability and have the potential to displace over time. Non-operative management of these unstable fractures may involve restricted weight bearing and significant rehabilitation. Frequent monitoring with X-rays is also necessary for displacement of the fracture. Operative stabilisation of these fractures may be appropriate to prevent displacement of the fracture. This may allow patients to mobilise pain-free, quicker.

**Methods and analysis:**

The study is a feasibility study to inform the design of a full definitive randomised controlled trial to guide the most appropriate management of these injuries. Participants will be recruited from major trauma centres and randomly allocated to either operative or non-operative management of their injuries. A variety of outcome instruments, measuring health-related quality of life, functional outcome and pain, will be completed at several time points up to 12 months post injury. Qualitative interviews will be undertaken with participants to explore their views of the treatments under investigation and trial processes.

Eligibility and recruitment to the study will be analysed to inform the feasibility of a definitive trial. Completion rates of the measurement instruments will be assessed, as well as their sensitivity to change and the presence of floor or ceiling effects in this population, to inform the choice of the primary outcome for a definitive trial.

**Ethics and dissemination:**

Ethical approval for the study was given by the South West—Central Bristol NHS Research Ethics Committee on 2nd July 2018 (Ref; 18/SW/0135). The study will be reported in relevant specialist journals and through presentation at specialist conferences.

**Trial registration number:**

ISRCTN10649958

Strengths and limitations of this studyThis is the first randomised multicentre study to investigate the treatment of high-energy unstable LC1 fractures.We are collecting a range of outcome measures at several time points to identify the most appropriate primary outcome for a definitive study.Qualitative interviews will provide valuable insights to identify challenges with recruitment and follow-up and inform the future definitive study design.Results of the TULIP feasibility will inform the design and conduct of a future multicentre Randomised Controlled Trial.

## Introduction

### Background

The Trauma Audit and Research Network (TARN) database indicate increasing numbers of pelvic ring fractures. In the financial year 2015/16, TARN recorded 6407 pelvic ring fractures in England and Wales of which half were associated with high-energy trauma. Fractures associated with a side or lateral compression force are the most common; a subgroup of these are called lateral compression type 1 (LC1). LC1 fractures make up approximately 60% of pelvic ring fractures,^1 2^ which equates to approximately 3800 patients a year within England and Wales. A proportion of pelvic fractures are sustained as a result of simple trips or falls and these are generally in the older person where bone quality is frequently poor. Stabilisation of fractures in elderly patients presents technical problems due to the difficulty in achieving adequate fixation in osteoporotic bone. The mortality during index hospital admission associated with LC1 fractures ranges from 5.1% to 8.6%.^1 2^

LC1 fracture patterns are a heterogeneous group of injuries, divided into those involving a complete or an incomplete fracture of the sacrum with or without an injury to the anterior pelvic ring.

The majority of LC1 fractures are considered stable enough to allow rehabilitation without later displacement. Numerous studies have shown complete sacral fractures to be present in 32%–50% of LC1 fractures.^3–5^ The combination of a complete sacral fracture and either unilateral or bilateral pubic rami fractures increases the degree of potential instability. Unstable LC1 fractures of the pelvis have a tendency to displace significantly over time.^6^ Bruce *et al*
5 reported 32% of patients with a complete sacral fracture and unilateral pubic rami fractures, and 68% of patients with a complete sacral fracture and bilateral rami fractures, went on to have significant displacement.

This, potentially unstable, subgroup of LC1 fractures may still be managed non-operatively. Patients would usually be allowed to mobilise as able although they may be advised to restrict the amount of weight they put through the injured side and will require walking aids provided by a physiotherapist. They also require frequent X-rays to monitor for any progression in fracture displacement. Patients with LC1 fractures are reported to spend up to 16 days in hospital following their injury^7^ and require significant rehabilitation following their discharge from acute care.^8^ These injuries can have significant implications for patients. Hoffmann *et al*
9 showed that even at 24 months postinjury, patients had not returned to their preinjury functional abilities. Aprato *et al*
8 found that 60% of the costs following pelvic injury were attributed to health-related work absence.

It may therefore be appropriate to surgically stabilise this subgroup of more severe, potentially unstable, LC1 fractures. This involves the insertion of metalwork to prevent displacement of the fractures. While patients will still require walking aids, their ability to mobilise may be improved. Tosounidis *et al*
7 carried out a non-randomised study comparing surgical versus non-surgical management of LC1 fractures. They found that patients had significantly decreased pain at 72 hours and were able to mobilise, pain-free, quicker following surgery. They also demonstrated a shorter length of stay in patients undergoing surgical fixation. However, Hagen *et al*
10 in a retrospective study looking at patients’ pain, narcotic use and mobility following surgical stabilisation of lateral compression fractures found no significant difference in these parameters between surgically and non-surgically treated groups.

Other advantages of treating these fractures surgically include a lower risk of fracture displacement and avoiding the risks associated with immobility, including chest or urinary tract infection, thrombosis and pressure sores. The disadvantages of treating LC1 fractures surgically are the risk of general anaesthesia, the physiological impact of surgery, the small risk of surgical site infection and of damage to the nerves that supply the bladder, bowel or leg muscles. As well as improving patients’ pain levels and functional abilities, surgery has been shown to provide economic benefits by reducing length of hospital stay and input required from healthcare professionals, which may outweigh the additional costs of surgery.

### Rationale

A survey on the management of LC1 fractures,^11^ although not specific to unstable LC1 fractures, indicated significant variation of practice in managing these fractures and agreement between surgeons was only achieved for one third of case studies.

Both Hagen *et al*
10 and Tosounidis *et al*
7 concluded that a randomised controlled trial of surgical versus nonsurgical management of LC1 fractures was needed. Currently there is no level 1 evidence available to guide clinicians as to the optimum management of these patients.

### Aim and objectives

The overarching aim is to perform a definitive trial to establish whether surgical or non-surgical management of unstable LC1 fractures is most appropriate. The aim of this feasibility study is to allow us to plan a full definitive trial by measuring recruitment, retention and follow-up rates and explore participant and staff views of the trial processes. Study objectives are shown in box 1.

Box 1Detailed study objectivesTo produce a Consolidated Standards of Reporting Trials diagram, reporting screening, recruitment, randomisation compliance and include allocation proportions by centre.To confirm the recruitment rates and percentage of eligible patients who agree to take part.To collect outcome data at fixed time points post injury to collate the completeness and spread of the data at different time points post injury.To identify the outcome measure to be used as the primary outcome on the basis of completeness of data, sensitivity to change over time, the presence of floor or ceiling effects and patient acceptability.To develop and refine methods for the collection of resource use data relating to both management pathways.To explore patient and staff views of randomisation, treatment and trial processes using qualitative interviews.

## Methods and analysis

### Trial setting

This multicentre trial will take place in 9 NHS Major Trauma Centres (MTC) which specialise in the treatment of pelvic injuries over 33 months. There are 22 MTCs across the UK currently where all patients with unstable pelvic injuries will be referred and assessed.

### Eligibility

All patients over 16 years of age presenting with an LC1 fracture including a complete sacral fracture will be assessed for inclusion in the study. A log of all patients meeting these criteria will be maintained. Patients will be excluded if they meet one of the following criteria:

Unable to be randomised within 72 hours of having capacity to comprehend the study information following arrival at the major trauma centre.Fragility fractures resulting from low-energy trauma (fall from less than standing height).Presenting medical condition which precludes surgical intervention.Unable to provide informed consent.

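### The bracketed threshold in the fragility exclusion, read literally, does not cover a simple fall from standing and so does not match the population named in the title

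*Protocol article*

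**What the plan says.** The inclusion rule under Eligibility in the protocol article is broad: "All patients over 16 years of age presenting with an LC1 fracture including a complete sacral fracture will be assessed for inclusion in the study". It sets no mechanism, no energy level and no upper age limit. Four exclusions follow. One concerns the time limit for randomisation, one a medical condition that rules out surgery, and one the inability to consent. The remaining one is the fragility exclusion: "Fragility fractures resulting from low-energy trauma (fall from less than standing height").

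The population is described in two other places. The title restricts the trial to LC1 injuries "in the non-fragility fracture patient". The Strengths and limitations list presents the study as the first multicentre randomised one in unstable LC1 fractures of the high-energy kind.

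The Background adds context: "A proportion of pelvic fractures are sustained as a result of simple trips or falls and these are generally in the older person". It notes the "difficulty in achieving adequate fixation in osteoporotic bone" and reports that "TARN recorded 6407 pelvic ring fractures in England and Wales of which half were associated with high-energy trauma".

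**The concern.** The fragility exclusion is the only criterion that can turn a broad inclusion rule into the population in the title. Its lead words do that job, but the bracket that makes them operational sets the cut-off one step too low. A fall from a chair or bed is from less than standing height. A trip while walking is not.

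The products of a feasibility study depend on who counts as eligible. The objectives (Box 1) include the percentage of eligible patients who agree to take part, the spread of the outcome data, and floor or ceiling effects. If some centres follow the bracket and others the lead words, these estimates mix two populations in proportions set by local reading of the rule. Differences between centres in eligible counts would then partly reflect wording. The definitive trial would inherit these figures.

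**Working it through.** **1. The texts side by side.**

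| Place in the protocol article | What it implies for a fall from standing |
|---|---|
| Title | Not intended, if the result is a fragility fracture |
| Strengths and limitations list | Not intended: the fractures are described as high-energy |
| Eligibility, lead words of the exclusion | Excluded, if judged a low-energy fragility fracture |
| Eligibility, bracket of the exclusion | Not covered: the fall is from standing height, not from less |
| Eligibility, inclusion rule | Admitted: no mechanism or energy requirement |
| Eligibility, other three exclusions | Silent on mechanism |

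The bracket is the only entry that gives a threshold, and it disagrees with the title, the high-energy description and its own lead words. No outside definition of a fragility fracture is needed to see this.

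**2. Which quantities are exposed.** The log covers everyone who meets the inclusion rule before exclusions, so its total is unaffected. The number eligible, the tally of exclusion reasons, the consent rate and the outcome distributions all come after the exclusion and are affected.

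**3. The plan's own figure.** Sample size assumes 120 eligible patients and 40% agreement, that is 0.40 × 120 = 48 recruits. The normal-approximation interval is 0.40 ± 1.96 × √(0.40 × 0.60 / 120) = 0.40 ± 0.088, or 31.2% to 48.8%. The exact binomial interval is 31.2% to 49.3%. The stated 31% to 49% is reproduced. The point does not turn on this figure, but it gives a scale.

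**4. Size.** The document does not give the share s of standing-height falls among LC1 fractures with a complete sacral fracture, so the effect cannot be computed. With s assumed for illustration only, and 40% consent throughout:

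| Assumed s | Eligible: 120 × s | Recruits: 48 × s |
|---|---|---|
| 5% | 6 | 2.4 |
| 10% | 12 | 4.8 |
| 20% | 24 | 9.6 |
| 30% | 36 | 14.4 |

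If consent among these patients differed by d from the 40% in the intended population, the pooled rate would move by s × d. To move it by the interval's half-width of 8.8 points, d would have to be 8.8 / 0.30 = 29 points at s = 30%, or 8.8 / 0.20 = 44 points at s = 20%. At s = 10% it would have to be 88 points, which is impossible from a base of 40%. The pooled consent rate is therefore fairly robust to a small admixture. The eligible count is not protected in this way, because it moves one for one with the patients admitted.

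**The case against.** The strongest reply is that the bracket only glosses the lead words. A low-energy fracture in osteoporotic bone after a simple trip is a fragility fracture on those words, and the title agrees. Patients are identified by their surgeon in centres that specialise in pelvic injuries, and a surgeon could exclude such a case by judgement. This stands, and it limits the point. A reader might infer that the rule admits exactly the patients the title leaves out. The text supports only that it can be read in two ways, one of which admits them.

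A reader might also infer from the Background that the study sets out to avoid simple trips and falls. That section says only that such fractures occur, generally in older people, and that fixation is difficult in osteoporotic bone. The intended population has to be taken from the title and the Strengths and limitations list.

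The exclusions for unfitness for surgery and inability to consent would remove some frail older patients. That is true, but neither replaces an energy threshold: a fit, consenting patient who fell from standing passes both.

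The harm is partly recoverable. No formal testing is planned, reasons for exclusion are reported, and injury characteristics are collected at baseline (Table 1). Whether these include mechanism of injury is not stated, so neither its presence nor its absence can be assumed.

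Finally, this is a condensed article. The full protocol and the flow diagram are not shown and may word the criterion differently, so different screening between sites is a conditional consequence. The published criterion would still need correcting.

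**Conclusion.** The point holds as an error in a stated eligibility threshold. Read literally, the bracket conflicts with its own lead words, with the title and with the high-energy description, and no other criterion closes the gap. The consequence is a possible mixed population in the eligible denominator, consent rate and outcome distributions. It depends on some centres applying the bracket rather than the intent, and on the full protocol carrying the same wording.

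No size can be attached. One might be tempted to take half of the 6,407 pelvic ring fractures, apply the 60% LC1 share, and conclude that 6,407 × 0.5 × 0.6 = 1,922 patients a year are at issue. The document does not support this. It does not say that the 60% holds among fractures that are not high-energy. The figure also ignores the complete sacral fracture (32% to 50% of LC1), the restriction to 9 centres and the other exclusions, and it treats every fracture that is not high-energy as a fall from standing. The shares tabulated in the working are assumptions with no anchor in the document, and the conclusion does not rest on them.

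**What to change.** Reconcile the bracketed threshold under Eligibility with the title and with the Strengths and limitations list. For the title, wording such as *fall from standing height or less* would suffice. It would not by itself deliver a high-energy population, because low falls from slightly above standing height would still enter. The sponsor should therefore also align either the high-energy description with the criterion or the criterion with the description.

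Notify all sites so that they apply one reading. Use mechanism of injury from the screening log and the baseline injury characteristics to report separately any standing-height falls already entered. If mechanism is not yet among those items, add it.

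The cost is a one-phrase amendment, a site notice and at most one data item. The eligible pool may be slightly smaller.

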### Recruitment

Patients eligible for inclusion in the study will be identified by their surgeon who will make the patient aware of the study and seek their agreement to consider participating. The study will then be fully discussed with the patient by a member of the research team at each site. Patients will be provided with a written information sheet explaining the purpose of the study and the treatments under investigation. They will be allowed sufficient time to consider the information provided and patients who agree to participate in the study will be asked to provide written consent. Patients who decline to participate in the study will be recorded on the screening log together with reasons for declining where provided.

To understand patient perceptions of the recruitment process, all patients that are approached regarding their potential participation in the study will be asked to complete a short questionnaire regardless of whether they consent to participate in the feasibility study. Patients will be asked to complete these questionnaires immediately following confirmation of their decision on participating in the study. Where this is not possible a copy of the questionnaire will be sent in the post by the local research team. Responses to these questionnaires will be confidential and patients will be identified only by their screening ID. The results of this questionnaire will be analysed as an ongoing process to help inform and develop the approach of further patients.

Figure 1 shows the flow of participants through the trial.

**Figure 1 F1:**
[figure not shown]
Study flow diagram.

### Allocation and blinding

Patients will be randomly allocated to the treatments on a 1:1 basis using a web-based randomisation procedure hosted by Bristol Randomised Trials Collaboration (a registered Clinical Trials Unit) with concealment prior to consent, but no blinding of participants or clinical staff to the allocation of treatment pathway. The trial statistician is responsible for producing the allocation sequence, stratified by recruiting centre and minimised on Injury Severity Score as an indicator of multiple injuries (<16 or>=16).

### Interventions

#### Surgical management

Surgical management will involve fixation of the pelvic fracture by a specialist pelvic surgeon at the earliest opportunity. As surgical fixation of these fractures is performed regularly in all participating centres the method of fixation and choice of implant will be left to the operating surgeon. Postoperative management and rehabilitation will be left to the discretion of the treating surgeon. Details on the surgery and subsequent rehabilitation will be collected as part of the study.

#### Non-surgical management

Non-surgical management will be left to the discretion of the treating surgeon. Any decision on restricted weight-bearing will be left to the treating surgeon. Rehabilitation including Physiotherapy and Occupational Therapy will follow usual practices. Details on the rehabilitation will be collected as part of the study.

### Outcomes

To assess the feasibility of the study design we will assess participant numbers such as recruitment rate, including numbers of patients meeting inclusion criteria and reasons for exclusion or declining where appropriate Compliance rates with allocated treatment and any reasons for not being able to comply. We will also look at follow-up rates, withdrawals, including reasons for withdrawal where appropriate in accordance with the Consolidated Standards of Reporting Trials diagram. We will look at the outcomes measures that are expected to be used in the full trial with particular interest in data completion rates, evidence of sensitivity to change (whether the score change over time) and whether the outcomes have ceiling or floor effects.

The following patient reported outcomes will be tested for use in a definitive study:

### Measures at baseline and follow-up

*Iowa Pelvic Score*: A measure specific to outcomes following pelvic injury.^12^ Shows good construct validity when compared with the physical component of the SF-36. This is also the preferred pelvic specific outcome measure by patients^13^ and the study patient advisory group.

*Oxford Hip Score*
14: A functional score for patients following hip injury and/or surgery. While not pelvic specific, the activities and symptoms included were felt to be relevant by our patient group.

*EQ-5D-5L*
15: A standardised instrument of health status.

*ICECAP-A*
16: A measure of capability for the general adult population for use in economic evaluation. It focuses on well-being in the broader sense, not just health status.

*Brief Pain Inventory*
17: Originally developed to measure pain in patients suffering from cancer. It has since been used in a variety of conditions. It allows patients to rate the severity of their pain as well as its influence on their psychological health and activity

All participants will complete these questionnaires at baseline, 2 and 6 weeks, 3 and 6 months following randomisation. Participants recruited in the first 12 months of the study will also complete questionnaires at 9 and 12 months following randomisation. Baseline data will be collected at recruitment. Participants will be able to complete their follow-up questionnaires in person, when attending an outpatient appointment, online or by post. Standard care for participants with these injuries would be for clinical review in an outpatient clinic at 6 weeks, 3 months and 12 months (see table 1).

**Table 1 T1:** Visit schedule

	Baseline	2 weeks* (+1 week)	6 weeks* (±1 week)	3 months* (±2 weeks)	6 months* (±3 weeks)	9 months* (±3 weeks)	12 months* (±4 weeks)
	Inpatient	Phone/online	Clinic	Clinic	Post/online	Post/online	Clinic
Demographics	✓						
Injury characteristics	✓						
Clinical review	✓	✓†	✓	✓			✓
Surgical details		✓‡					
Rehabilitation		✓	✓	✓	✓	✓	✓
Adverse events	✓	✓	✓	✓	✓	✓	✓
Iowa Pelvic Score	✓§	✓	✓	✓	✓	✓	✓
OHS	✓§	✓	✓	✓	✓	✓	✓
EQ-5D-5L	✓§	✓	✓	✓	✓	✓	✓
ICECAP-A	✓	✓	✓	✓	✓	✓	✓
BPI	✓§	✓	✓	✓	✓	✓	✓
TUAG			✓	✓			✓
Resource use			✓	✓	✓	✓	✓

*From date of randomisation.

†Non-operative group only.

‡Surgical group only.

§Preinjury and postinjury.

BPI, Brief Pain Inventory; EQ-5D-5L, Euroquol - 5 Dimension - 5 level; ICECAP-A, ICEpop Capability measure for Adults; OHS, Oxford Hip Score; TUAG, Timed Up and Go.

At these time points, in addition to the questionnaires, participants will complete a Timed Up and Go assessment.^18^ This is an assessment of a participant’s physical walking ability and involves being timed to stand from a chair, walk a distance of 3 m and return to sit in the chair. Where possible this will be completed by an assessor blinded to the participant’s treatment allocation. Completeness of this assessment will be recorded to inform the appropriateness of its use in a definitive trial.

Data obtained as part of the study will be entered on to a secure password protected online REDCap database.

